### Qualitative study data

In the qualitative process analysis of the study the aim is to explore and explain how the specific programme works for those involved, rather than focusing on endpoints [45]. Data will be generated by interviews with patients and family members 1 year after inclusion in the study. Dyadic interview will examine the interaction between the participants, and thereby obtain details of discrepancies and similarities between them [46].

Interviews will initially be guided by a semi-structured interview guide developed on the basis of knowledge from earlier studies and the FAM-III questionnaire. The interview guide will change dynamically according to theoretical sampling and therefore data collection and analysis of previous interviews will guide the following interview in a constant comparative method throughout the entire research process [47]. Approximately 20 patients (10 from each arm) and their family members will be included consistent with theoretical sampling and hence preliminary inclusion criteria’s are not desirable nor possible. Further participants can be included if theoretical saturation is not achieved [47]. All interviews will be conducted at the patient’s home or at the hospital according to the patient and the family member’s wish. Participants will be excluded if they for any reason are not able to manage a 45–60 minute interview.

### Statistical analysis

We will present and compare the baseline demographics as well as clinical and diabetes-related characteristics of the intervention and the control group. The statistical comparison will be conducted on the basis of *t* tests or analysis of variance as appropriate for comparing means and χ^2^ tests for categorical or binary data. The primary outcome will be tested by constructing a 90 % two-sided confidence interval for the difference of the means of HbA_1c_ between the intervention and the control group. We use the lower bound to determine non-inferiority. Other outcomes will be tested with superiority analyses such as linear or logistic regression analysis. For observed differences we will consider a *P* value less than 0.05 as statistically significant.

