### Study data

All study data will be collected in connection with the annual comprehensive check-up in the outpatient clinic at the baseline-screening visit, as well as 12, 24 and 36 months after baseline. Data will be obtained from medical records, laboratory databases, self-reported patient questionnaires and face-to-face by the primary investigator who does not take part in the treatment or care of the patients. All data will be registered in an Epidata database [32]. The database is stored at Gentofte Hospital in a secure purpose-designed password-protected web-based file system.

The primary outcome is the difference in mean HbA_1c_ between the two groups measured at 12-, 24- and 36-months follow-up. The secondary outcome is the proportion of patients who meet the set of Danish standard indicators reflecting quality of care at 12, 24 and 36 months follow-up [33]. These indicators cover seven areas, including HbA_1c_, blood pressure, low density lipoprotein, albuminuria, fundus photography, foot examination, smoking status and proper treatment and control of these factors. The indicators are primarily based on process variables, but do include a few numerical variables.

Other outcomes are listed below:

*Clinical characteristics:* Blood pressure, weight and body mass index.

*Diabetes-related laboratory parameters and characteristics:* C-peptide, insulin, lipids, liver function tests, kidney function tests, electrolytes, coagulation factors, thyroid-stimulating hormone, cardiovascular biomarkers, vitamin D, urine albumin/creatinine ratio, and registration of diabetes-related medication.

*Healthcare professionals’ experiences with shared care:* A questionnaire evaluating the experiences of the participating GPs and the endocrinologists after the completion of the 12- and 36-month follow-up periods.

*Patient-reported outcomes:* Estimation of general quality of life, diabetes-related symptoms, alcohol consumption patterns as well as patients’ experiences of family network and function.

The four questionnaires used are:

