### Population size calculation

A power calculation was conducted according to criteria for non-inferiority trials [42, 43], and based on the primary outcome measure Hb_A1c_ at 12-month follow-up. The non-inferiority margin was set at 0.4 % (1 % is approximately 11 mmol/mol) based on both clinical judgement and a guideline from the European Medicines Agency identifying the non-inferiority margin for HbA_1c_ above 0.3 % (3 mmol/mol) [44]. The standard deviation of HbA_1c_ was set at 10 mmol/mol, based on a recent study on patients with risk stratification level 2 attending our outpatient clinic [31]. With a non-inferiority margin at HbA_1c_ 4.4 mmol/mol, an alpha of 0.05 and a power at 0.8, as well as an estimated dropout rate of 10 %, the sample size has been estimated to 140 participants.

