## Discussion

The overall objective of this study is to evaluate whether sharing general and specialised healthcare is comparable to the specialised care delivered in a hospital-based outpatient setting for patients with T2D who are at intermediate risk of or are already having incipient diabetic complications. The hypothesis is that the changes in HbA_1c_ at 12-, 24- and 36-month follow-up are comparable between the intervention and the control group. According to previous studies the evidence for shared care in different chronic diseases, including T2D, is not clear [20]. Testing new shared care models as a way of alternative organisation of care for patients with T2D is therefore important. The majority of studies on shared care for patients with T2D have been conducted 15–20 years ago. However, the increasing number of patients with T2D who are referred to the outpatient clinics as well as the development and improvements of electronic systems, clinical databases and communication channels during the last decades has made it highly relevant to test shared care models in new settings. Shared databases and electronic correspondence across the interface of the primary and secondary healthcare sectors are expected to blur the boundaries between the different healthcare sectors.

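### The primary HbA1c comparison reads as an unadjusted difference of follow-up means; adjusting for the baseline HbA1c already scheduled would gain precision at no extra data cost

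*Protocol article*

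**What the plan says.** In the protocol article, Statistical analysis specifies for the primary outcome a 90 % "two-sided confidence interval for the difference of the means of HbA_1c_ between the intervention and the control group". It names no model and no covariate there; linear and logistic regression are mentioned only for the remaining outcomes.

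Study data defines the primary outcome as a between-group difference in mean HbA1c at 12, 24 and 36 months. The same section says that study data are collected "at the baseline-screening visit, as well as 12, 24 and 36 months after baseline". HbA1c is also one of the parameters in the risk stratification that decides eligibility (Table 1), so each randomised patient should have a baseline value.

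Population size calculation sizes the trial on HbA1c at 12 months: "The standard deviation of HbA_1c_ was set at 10 mmol/mol". This is the spread of HbA1c itself, with no reduction for baseline.

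The Discussion uses another wording: "The hypothesis is that the changes in HbA_1c_ at 12-, 24- and 36-month follow-up are comparable between the intervention and the control group".

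**The concern.** Baseline HbA1c can be expected to predict later HbA1c, and it is free to use. A comparison of follow-up means leaves the variation that baseline explains in the standard error. In a non-inferiority trial, the width of the interval largely decides whether the margin can be excluded. With 140 patients and a margin of 4.4 mmol/mol, a narrower interval is worth having.

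The wording also leaves some doubt about the estimator. A difference in follow-up means and a difference in mean change estimate the same quantity under randomisation, but with different precision, so one data set could meet the margin under one and miss it under the other. Naming one estimator in advance removes that choice, which matters more because allocation is known after the screening visit.

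**Working it through.** **Inputs.** From Population size calculation: "With a non-inferiority margin at HbA_1c_ 4.4 mmol/mol, an alpha of 0.05 and a power at 0.8"; standard deviation 10 mmol/mol; "an estimated dropout rate of 10" %; and "the sample size has been estimated to 140 participants". Allocation is 1:1 (Randomisation). That section does not say whether alpha is one- or two-sided; one-sided 0.05 matches the 90 % two-sided interval. The true difference is taken as zero. The correlation r between baseline and follow-up HbA1c is not in the documents, so 0.3 to 0.6 is assumed.

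**The plan's own figure.** n per arm = 2 × 10² × (1.645 + 0.842)² / 4.4² = 63.9, rounded up to 64, or 128 in total. Allowing for dropout, 128/0.9 gives 143 and 128 × 1.1 gives 141. Both are close to 140. One-sided alpha of 0.025 would need 82 per arm, 164 in total and 183 with dropout, which does not match. The stated number therefore comes from an unadjusted two-sample comparison at one-sided 0.05.

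**Power and width as planned.** Evaluable per arm: 140 × 0.9 / 2 = 63.
- Standard error = 10 × √(2/63) = 1.78 mmol/mol.
- Half-width of the 90 % interval = 1.645 × 1.78 = 2.93 mmol/mol.
- Power = Φ(4.4/1.78 − 1.645) = 79.5 %.

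**With baseline adjustment.** The residual standard deviation becomes 10 × √(1 − r²) and replaces 10 in the same formulas. For comparison, an analysis of plain change scores has standard deviation 10 × √(2(1 − r)), if the baseline standard deviation is also 10 (assumed).

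| Assumed r | ANCOVA SD | 90 % CI half-width | ANCOVA power | Change-score power |
|---|---|---|---|---|
| 0 (no gain) | 10.00 | 2.93 | 79.5 % | 54.0 % |
| 0.3 | 9.54 | 2.80 | 82.7 % | 67.1 % |
| 0.5 | 8.66 | 2.54 | 88.6 % | 79.5 % |
| 0.6 | 8.00 | 2.34 | 92.5 % | 86.8 % |

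Adjustment gains at every value of r above zero. Plain change scores lose power against follow-up means below r = 0.5, equal them at 0.5 and gain only above it. Simply switching to the Discussion's wording is therefore not a safe substitute.

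**Follow-up or change makes no difference after adjustment.** If change = a + b·arm + c·baseline, then follow-up = a + b·arm + (c + 1)·baseline. The arm coefficient b and its interval are the same.

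**How far chance imbalance carries.** With a baseline standard deviation of 10 (assumed), the baseline difference between arms has standard error 1.78 mmol/mol at 63 per arm. About r times any such difference passes into the unadjusted estimate. A one-standard-error imbalance thus moves it by about 0.53 (r = 0.3), 0.89 (r = 0.5) or 1.07 (r = 0.6) mmol/mol, against a margin of 4.4.

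**The case against.** The strongest reply is that covariates belong in the statistical analysis plan, which is not shown. The article never says that the comparison is unadjusted, and an ANCOVA also yields a difference of means. It is true that the unadjusted reading is inferred. But the article does state the primary estimator, reserves regression for other outcomes and sizes the trial on the raw standard deviation. These statements agree with each other, so the point is a better method for a stated choice, not a missing detail.

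Three stronger readings are tempting, and the documents do not support them.
- **That the trial is underpowered.** It is not: the sample size was set for the unadjusted analysis and essentially meets the 80 % target.
- **That baseline imbalance biases the result or inflates the error rate.** Under randomisation the unadjusted difference is unbiased on average and its interval already allows for chance imbalance. Only about r times the baseline difference carries through, so comparing the full 1.78 with the margin would overstate it.
- **That the document commits itself to two conflicting analyses.** The outcome definition, sample size and analysis sections agree. The reference to changes is one loosely worded sentence in the Discussion.

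It also stands that the size of the gain rests on an undocumented correlation. Eligibility excludes HbA1c above 75 mmol/mol (Table 1), which may lower that correlation. At r = 0.3 the gain is only about 3 percentage points.

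**Conclusion.** The point holds as a recommended improvement, not as an error in the plan's figures. As written, the primary analysis reads as an unadjusted comparison of follow-up means. At 63 evaluable per arm, ANCOVA would add about 3, 9 or 13 percentage points of power for r = 0.3, 0.5 or 0.6, and narrow the 90 % interval by about 4 %, 13 % or 20 % (2.80, 2.54 or 2.34 against 2.93). These figures assume a standard deviation of 10 mmol/mol, a true difference of zero, one-sided alpha of 0.05 and 10 % dropout. They apply to 12 months; the gain at 24 and 36 months depends on the correlations at those visits, which are also not given.

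**What to change.** Define the primary estimate as the arm coefficient, with its 90 % confidence interval, from ANCOVA of 12-month HbA1c on arm and baseline HbA1c; 12 months is the time point used for sizing. Obtain the 24- and 36-month estimates with the same baseline adjustment. Report the unadjusted difference of means as a sensitivity analysis. Align the wording in Study data, Statistical analysis and the Discussion so that all three describe this one estimator.

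The cost is a change of wording, fixed before outcome data are compared by arm. Baseline HbA1c is already a scheduled measurement, so no extra visit, test or patient is needed, and the sample size of 140 can stay.

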**Methods:**

The study is designed as a randomised controlled trial. The shared care model will be tested during a period of 3 years, with data collection at baseline and at 12, 24 and 36 months. All patients will be offered four medical visits a year; the shared care intervention consists of one annual comprehensive check-up at the outpatient clinic and three quarterly visits at the general practitioners’ office. The control group will be followed with four quarterly visits at the outpatient clinic, including an annual comprehensive check-up. In the outpatient clinic, the patients will be treated by a specialised diabetes team, including an endocrinologist. On the basis of a predefined stratification model, we will recruit patients stratified to be at intermediate risk of or already having incipient diabetic complications. We plan to include 140 patients. The primary outcome is glycated haemoglobin. Other outcome measures include (1) the proportion of patients who meet the Danish standard indicators reflecting quality of care; (2) quality of life measured by Short Form 36; and (3) the functionality of the patients’ families measured by Family Assessment Measure III. The experiences of the patients and families when participating in the shared care program will be explored by collecting dyadic interviews.

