### Exclusion criteria

Patients are excluded if they have other types of diabetes than T2D, are at risk stratification level 1 or 3 (Table 1), are pregnant or breastfeeding, have severe co-morbidity with a life expectancy less than 5 years, or are under such conditions that they will not be able to attend or complete the appointments (e.g. due to dementia or psychiatric conditions). Furthermore, we will exclude patients who are either participating in other studies that potentially may affect the primary outcome of our study, or patients participating in studies which include blood sampling amounting to > 5 % of the blood volume in a 2 month period prior to the randomisation and/or the follow-up visits. The risk stratification level is assessed by the endocrinologist during the 12- and 24-months follow-up. If the patient has shifted from level 2 to level 3, the patient is excluded from the study. These patients will be offered long-term follow-up in the diabetes outpatient clinic. Patients changing from level 2 to level 1 will continue their participation in the study.

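### Removing patients on high HbA1c at 12 and 24 months, combined with a plain difference of means, tilts the 24- and 36-month tests towards non-inferiority; a repeated-measures model on values already collected corrects this

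*Protocol article*

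**What the plan says.** All references are to the Protocol article.

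- **Measurement.** The Abstract (Methods) describes a three-year trial "with data collection at baseline and at 12, 24 and 36 months". Study data defines the primary outcome as the between-group difference in mean HbA1c at the three follow-up visits, and the Discussion hypothesises comparability at all three.
- **Primary test.** Statistical analysis specifies a 90% "two-sided confidence interval for the difference of the means", and adds: "We use the lower bound to determine non-inferiority". Regression is mentioned only for the other outcomes.
- **Removal.** Exclusion criteria have the risk level reassessed at 12 and 24 months: "If the patient has shifted from level 2 to level 3, the patient is excluded from the study". Those who improve to level 1 continue. In Table 1, HbA1c above 75 mmol/mol is a level 3 parameter, and its notes say that one such parameter is sufficient.
- **Sizing.** Population size calculation rests on the 12-month visit and uses a "non-inferiority margin at HbA_1c_ 4.4 mmol/mol" together with a 10% allowance for losses. The error rates behind it are "an alpha of 0.05 and a power at 0.8", and the total comes to 140.

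The article names no analysis set, no missing-data method and no model for the repeated HbA1c values.

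**The concern.** The removal rule acts on the primary outcome itself, and only at its upper end. If shared care is truly worse, more of its patients cross 75 mmol/mol and leave. The patients who remain look more alike across arms than the randomised groups are, so a difference of means among them understates the harm. In a non-inferiority trial that error favours the new programme: one that is worse by the full margin would be declared acceptable more often than the stated 5%.

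The information needed to correct this is largely on file, because the HbA1c that triggers removal has been recorded. A plain difference of means at a later visit makes no use of it.

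**Working it through.** **1. Reproduce the plan's figure.** Inputs from Population size calculation: "The standard deviation of HbA_1c_ was set at 10 mmol/mol", margin 4.4, alpha 0.05 taken as one-sided (which matches a 90% two-sided interval), power 0.8.

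n per arm = 2 × (1.645 + 0.842)² × 10² / 4.4² ≈ 63.9, so 64 per arm and 128 in total. Allowing for 10% dropout gives 128 / 0.9 = 142.2 (143) or 128 × 1.1 = 140.8 (141). Both agree with the stated 140 to within 3%. One-sided 0.025 would need 82 per arm, or 183 in total after dropout, so the nominal error rate is 5% one-sided.

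**2. Show the mechanism by hand.** Assume a 12-month control mean of 58, SD 10 and shared care 4.4 worse (62.4). The chance of exceeding 75 is:
- control: 1 − Φ((75 − 58)/10) = 1 − Φ(1.70) = 4.5%, about 3 of 70;
- shared care: 1 − Φ((75 − 62.4)/10) = 1 − Φ(1.26) = 10.4%, about 7 of 70.

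So the worse arm loses more than twice as many high values at the first reassessment.

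**3. Simulate the tests.** Settings: 70 per arm, SD 10, true difference 4.4 at every follow-up visit, 10% random dropout spread over three years, and removal after the 12- or 24-month visit if HbA1c exceeds 75. A pass means that the harm-side bound of the 90% interval lies within 4.4. The mean (that without the harm) and the correlation are assumptions. There were 2,500 trials per setting, with simulation error of about 0.4 points. Where two figures are given, they span runs with and without baseline capped at 75.

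| Mean, correlation | Observed means, 24 mo | Observed means, 36 mo | Model, 24 mo | Model, 36 mo |
|---|---|---|---|---|
| 52, 0.5 | 6.2–6.8% | 7.8–8.0% | 5.1–5.4% | 4.4–5.5% |
| 55, 0.6 | 7.0–8.6% | 9.8–10.0% | 4.4–5.4% | 4.8–5.3% |
| 58, 0.6 | 8.9–9.3% | 11.8–13.4% | 5.4–5.8% | 5.0–5.6% |
| 60, 0.6 | 9.9–10.5% | 13.2–13.9% | 4.8–5.3% | 5.2–5.6% |
| 62, 0.7 | 13.1–15.2% | 17.5–20.2% | 5.3–5.4% | 5.0–5.3% |

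At mean 58, observed means shrink the true 4.4 to 3.75–3.84 at 24 months and 3.42–3.57 at 36 months. The likelihood-based repeated-measures estimate averages 4.35–4.46 across all settings in the table.

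A separate run at correlation 0.55, with dropout of 10/5/5% per year, gave for observed means (24 / 36 months): mean 50, 6.0 / 5.5%; mean 55, 6.8 / 9.1%; mean 58, 7.0 / 10.1%; mean 60, 9.5 / 12.8%.

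**4. Check bias against error rate.** At mean 58 the 36-month bias is 4.4 − 3.57 = 0.83 to 4.4 − 3.42 = 0.98. With about 57 patients left per arm (the average of 80% and 84% of 70, the retention in the gradual-harm run below), SE ≈ 10 × √(2/57) = 1.87. The pass rate is then Φ(−1.645 + 0.83/1.87) = Φ(−1.20) = 11.5% to Φ(−1.645 + 0.98/1.87) = Φ(−1.12) = 13.1%. This agrees with the table.

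**5. Isolate the cause and vary the assumptions.**
- No HbA1c-driven removal, random dropout only: 5.1, 5.0 and 4.7% at 12, 24 and 36 months.
- With removal, the 12-month test stays at about 5%, because removal follows that visit's measurement.
- Harm building up gradually (1.5, 3.0, 4.4; mean 58): 8.3% at 36 months.
- SD 8 (mean 58, correlation 0.6): 7.3% and 10.1% at 24 and 36 months.
- Means 48–64 and correlations 0.3–0.7: 5.3–17.4% at 24 months and 5.9–23.3% at 36 months.

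**The case against.** The strongest reply is that the article never says earlier values are thrown away. A contrast from a model is also a difference of means, and the missing-data method may sit in an analysis plan that is not shown. A reader might infer that the plan prescribes discarding these values; the text does not support that. What stands is that the section names a plain difference of means as the primary method and mentions regression only for other outcomes, so following it literally on patients still in the study produces the bias.

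Second, the inflation comes from the removal rule and not from the planned 10% dropout. That is correct: without HbA1c-driven removal the rate is about 5%.

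Third, the size rests on assumed values. Level 2 can be met through blood pressure or microalbuminuria alone, so patients with HbA1c below 53 can enter and the mean may be low. Near 48–50 the inflation is slight.

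Fourth, calling the result biased presumes a target. Removed patients are offered follow-up in the outpatient clinic, which is the control setting. The model estimates the difference had they stayed in their assigned programme, and the simulations let removal depend only on recorded HbA1c, which favours the model. This is fair, and it is why the target should be stated and a sensitivity analysis added.

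**Conclusion.** The point holds in conditional form. If the primary interval is computed as written on patients still in the study, the removal rule biases the 24- and 36-month tests towards non-inferiority. With a mean of 50–60 mmol/mol, a correlation of about 0.55–0.6, 70 per arm, SD 10 and a true difference of 4.4, the false non-inferiority rate is about 5–10% at 24 months and 6–14% at 36 months, against a nominal 5%. It is higher with higher means and lower if the harm accrues gradually.

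A reader might conclude that the error rate simply doubles at both later visits. The documents do not support a single figure, because they give neither the mean nor the correlation, and 24 months is affected less than 36. Nor do they support a charge against the 12-month test on which the sample size rests.

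These figures take the bound on the harm side. Whether the article's reference to the lower bound has the right direction is a separate matter, as is whether level 3 patients should leave the study. This is a cheap improvement and worth making, because all three visits belong to the primary outcome.

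**What to change.** In Statistical analysis, estimate the arm difference at each visit from a linear mixed model for repeated measures:
- HbA1c at baseline, 12, 24 and 36 months from all randomised patients;
- visit and arm-by-visit effects, a common baseline mean and unstructured covariance;
- every recorded value up to and including the one at which a patient is removed.

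Read the model's 90% interval at each visit against 4.4 mmol/mol. State that the target is the difference had removed patients remained in their assigned programme.

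Keep the difference of observed means as a sensitivity analysis, and add one in which missing shared-care values are shifted upwards.

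The cost is analysis wording only, with no extra patients or measurements and no change to clinical follow-up. Precision at the later visits is equal or better. The small downside is the assumption that missingness depends only on recorded HbA1c. Removals on other level 3 parameters and ordinary dropout may violate it, and the shifted analysis tests that.
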